### 2.3 Intervention

Participants will receive tACS targeting one of three cortical regions: the ACC, DLPFC, or insula. These targets were selected based on their involvement in the triadic model of craving, representing the impulsive, reflective, and interoceptive systems, respectively (Christie and Bechara, 2020).

Stimulation will be delivered at fixed frequencies supported by the literature on oscillation-specific effects of tACS. The DLPFC will be stimulated at 10 Hz (alpha frequency), while the ACC and insula will receive 6 Hz (theta frequency) stimulation. This frequency choice aligns with prior findings suggesting functional specificity of alpha oscillations in top-down control and theta oscillations in cognitive conflict and interoception (Stecher et al., 2021; Vogeti et al., 2022; Wischnewski et al., 2023).

The stimulation intensity will vary by region, reflecting anatomical depth and field modeling data. For the DLPFC and ACC, the peak-to-peak current will range between 1.5 and 2 mA. However, due to its deeper cortical location, the insula will be stimulated with higher intensities, between 8 and 9 mA peak-to-peak. This is consistent with recent human studies demonstrating the feasibility and tolerability of higher-output tACS for reaching deep brain structures (Shan et al., 2023; Wischnewski et al., 2023). All sessions will last 20 min and occur once daily over seven consecutive days.

Individualized modeling will be conducted using T1-weighted structural MRI scans to generate finite element models (FEMs). Electrode montages will then be optimized using ROAST (Realistic vOlumetric Approach to Simulate Transcranial electric stimulation) (Huang et al., 2019), allowing simulation of electric field distributions within each participant’s head. The modeling will ensure that target field strengths exceed 0.4 mV/mm, a threshold associated with effective neuromodulation (Wischnewski et al., 2023). If predicted intensities fall below this threshold in any region, montage adjustments will be implemented prior to stimulation. HD-Explore, an online visualization tool, will be used to confirm current flow patterns and facilitate replication by other researchers.

In the sham condition, electrodes will be placed according to the international 10–20 system (F3/F4). The current will ramp up over 30 s and then be reduced to zero for the remainder of the session, followed by a final 30-s ramp-down. This approach preserves blinding by mimicking the initial somatosensory sensations associated with active tACS (Ljubisavljevic et al., 2022).

All sessions will be conducted by trained personnel, and adverse events will be monitored throughout.

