## 2 Methods

### 2.1 Study design

This randomized, double-blind, sham-controlled, parallel-group trial is designed to investigate the effects of fixed-frequency transcranial alternating current stimulation (tACS) on food cravings, inhibitory control, and associated neural oscillations. The study includes participants with and without food addiction, classified according to the Yale Food Addiction Scale 2.0 (YFAS 2.0).

Participants classified as food-addicted (FA+) will be randomly assigned to one of four intervention arms: (1) active tACS targeting the anterior cingulate cortex (ACC) at a theta frequency of 6 Hz, (2) active tACS targeting the dorsolateral prefrontal cortex (DLPFC) at an alpha frequency of 10 Hz, (3) active tACS targeting the insula at a theta frequency of 6 Hz, or (4) sham tACS serving as a placebo control.

Participants classified as non-addicted (FA-) will be assigned to a separate fifth group. This group will follow a within-subject, counterbalanced crossover design in which each participant receives both active and sham stimulation across two sessions. Sessions will be scheduled on consecutive days, with a 24-h interval, and the stimulation order randomized to mitigate order effects. This approach enables within-subject comparison of stimulation effects in individuals without food addiction and allows for additional between-group analyses contrasting FA+ and FA- responses. Furthermore, the crossover approach in the FA- group is selected to reduce unnecessary stimulation exposure and focus statistical power on the primary FA+ comparisons, while still enabling exploratory within-subject analyses in non-addicted participants.

This design allows for direct comparisons between active and sham conditions and across cortical targets while also enabling exploration of craving-related network dynamics in the presence and absence of FA.

Randomization will be conducted using a computerized block randomization algorithm, stratified by food addiction status (FA+ vs. FA-). To ensure allocation concealment, the randomization sequence will be generated by a researcher not involved in data collection or analysis. All participants, tACS administrators, and outcome assessors will remain blind to group allocation throughout the study.

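### Sham uses one F3/F4 placement while active montages are individually optimised for three targets, which conflicts with the claim that tACS administrators stay blind and leaves at least two active-versus-sham contrasts without a site-matched control

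*Protocol article*

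**What the plan says.** Four statements in the protocol article bear on this point.

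- **Sham placement (section 2.3):** "In the sham condition, electrodes will be placed according to the international 10–20 system (F3/F4". No other sham placement is described. The sham current ramps up over 30 s, goes to zero, and is followed by a closing 30 s ramp-down. The level reached by the ramp is not given.
- **Active placement (section 2.3):** "Individualized modeling will be conducted using T1-weighted structural MRI scans to generate finite element models (FEMs". Then "Electrode montages will then be optimized using ROAST", and "If predicted intensities fall below this threshold in any region, montage adjustments will be implemented prior to stimulation". Currents also differ by target: "For the DLPFC and ACC, the peak-to-peak current will range between 1.5 and 2 mA", whereas "the insula will be stimulated with higher intensities, between 8 and 9 mA peak-to-peak".
- **Arms (section 2.1):** the food-addicted (FA+) participants are randomised to three active targets or to a single comparator, listed as "4) sham tACS serving as a placebo control".
- **Blinding (section 2.1):** "All participants, tACS administrators, and outcome assessors will remain blind to group allocation throughout the study". The only means of blinding that section 2.3 offers is that the ramp imitates the skin sensation at the start of active stimulation.

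**The concern.** There are two separate problems.

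The first is a conflict between statements. Electrode position cannot be hidden from the person who places the electrodes. If sham is always at F3/F4 and active placements are tailored to the individual and the target, position carries information about allocation. Imitating the ramp sensation is aimed at the participant and does nothing for the administrator.

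The second is the quality of the control. One sham site stands as comparator for three active targets. Where the sites differ, an active-versus-sham contrast compares stimulation plus one montage with no stimulation plus another. Section 2.4 makes self-reported craving (S-FCQ and FCI), measured just before and after sessions, part of the primary outcome, and such a measure is open to expectation and to what the participant feels on the scalp. Montage is tied to arm by design, so no analysis can separate the two afterwards.

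**Working it through.** The plan gives no figure to reproduce on this point. The check sets the statements side by side, with a little arithmetic.

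**1. Can the person placing electrodes infer allocation from position?**

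| Arm (FA+) | Placement stated in section 2.3 | Distinguishable from F3/F4? |
|---|---|---|
| ACC, theta | individually optimised, adjusted if the modelled field is too low | yes, clearly |
| Insula, theta | as above | yes, clearly |
| DLPFC, alpha | as above | less certain; a frontal montage may resemble F3/F4 |
| Sham | F3/F4 for everyone | – |

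The last column is inference: the article does not list the active electrode positions. A standard placement used for one arm only, set against individual placements for the others, is nevertheless recognisable in at least the first two rows. This is incompatible with the administrator part of the blinding sentence unless someone else places and covers the electrodes. No such step is described.

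**2. How many contrasts lack a site-matched sham?** There are three active targets and one sham site, which can resemble at most one of them. 3 − 1 = 2, so at least two of three contrasts (ACC and insula) are unmatched.

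**3. What do the stated currents show?** The insula current relative to DLPFC/ACC is:

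- lowest: 8 / 2 = 4.0
- highest: 9 / 1.5 = 6.0
- midpoints: 8.5 / 1.75 = 4.9

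These ratios are between active arms. They show that sensation is unlikely to be the same in all three, so a single sham procedure can hardly imitate each equally well. They do not give a sham-to-active ratio, because the sham ramp level is not stated.

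**4. What would spreading the sham arm over three montages cost in precision?** Section 2.2.5 puts 140 participants in four FA+ groups: 140 / 4 = 35 each. Then 35 / 3 = 11.7, so the split is 12/12/11.

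For a difference in means with a common SD, the standard error is proportional to √(1/n₁ + 1/n₂). With full enrolment:

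- pooled sham, 35 v 35: 1/35 + 1/35 = 0.0571
- site-matched, 35 v 12: 1/35 + 1/12 = 0.1119; √(0.1119/0.0571) = 1.40
- site-matched, 35 v 11: 1/35 + 1/11 = 0.1195; √(0.1195/0.0571) = 1.45

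The pooled comparison loses no sample size. A strictly site-matched contrast has a standard error 40–45% larger, which makes it suitable as a supportive analysis only.

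**The case against.** The strongest reply is that this is a condensed article. Coded sham modes or separate set-up staff may be in the full protocol, and a single-site sham is a recognised design choice. In part this stands. Nothing can be concluded from the article's silence on how the device is operated, so the argument here rests on position alone. Separate staff who place and cover the electrodes could restore administrator blinding. That would not cure the site mismatch, and coded files alone do not hide where electrodes sit.

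Four stronger readings are tempting, and the article supports none of them.

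- **That the double-blind claim fails altogether.** FA+ participants are in parallel arms and each experiences one montage, so site alone does not tell them their arm. Assessor blinding is not contradicted either, since section 2.1 names assessors and administrators as separate roles.
- **That unblinded administrators collect the craving data.** The article does not say so. The craving measures are questionnaires and the Go/No-Go task is computerised.
- **That sham current falls short of active current four- to six-fold.** That ratio compares active arms with one another.
- **That the bias amounts to some fraction of the planned effect size.** Any such figure would rest on an assumed shift in craving for which the article gives no basis.

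The closing ramp-down after the current has reached zero is a point of wording. It needs clarifying but has no bearing on montage or on who is blind.

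**Conclusion.** The point holds in a limited form. Sections 2.1 and 2.3 conflict on administrator blinding: a fixed F3/F4 sham beside individually optimised active montages lets staff who place electrodes often recognise sham, most surely against ACC and insula. In addition, at least two of the three active-versus-sham contrasts have no site-matched control, so part of any difference in self-reported craving could come from montage and sensation. The direction and size of that effect cannot be computed from the article.

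This rests on two assumptions: that the staff called administrators place the electrodes or see them in place, and that ACC and insula montages do not coincide with F3/F4. It should be settled before enrolment, because the sham placement cannot be repaired afterwards.

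**What to change.** **Preferred change.** Keep one sham arm of 35, but randomise its participants about 1:1:1 (12/12/11) to the ACC, DLPFC or insula montage, each with their own ROAST-optimised placement. Have the independent researcher who already generates the sequence prepare coded active/sham device files. Position then no longer separates active from sham, although the operator may still see which target is in use, and the text should say so. Keep the pooled sham arm as the primary comparator and treat site-matched contrasts as supportive. Ask participants and operators to guess the allocation, and report the answers.

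**If this is not done.** Limit the blinding sentence in section 2.1 to participants and outcome assessors, and state that operators do not collect outcomes.

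**In either case.** The sponsor must reconcile the section 2.3 text on the sham current course: the ramp level in relation to the differing active currents, and the ramp-down that follows zero current. No setting is proposed here.

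**Cost.** No extra participants and no extra scan are needed, since structural MRI is already scheduled for Day 0 (Figure 1 legend). The work is modelling for the sham participants where not already planned, file preparation and a short question. The price is a sham arm that is no longer procedurally uniform, and only 11–12 sham participants for each strictly site-matched contrast. The fallback costs only a change of text, but leaves the site mismatch in place.

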### 2.4 Outcome measures

The primary outcomes of this study are changes in food craving intensity and inhibitory control following the tACS intervention. Craving will be assessed using the State Food Craving Questionnaire (S-FCQ) and the Food Craving Inventory (FCI), both administered before and immediately after stimulation sessions on Days 1 and 5 (Figure 1). Inhibitory control will be evaluated using a computerized Go/No-Go task at the same time points. These behavioral measures will provide insight into the acute and cumulative effects of tACS on craving regulation and impulse control.

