This protocol builds on earlier work showing that neuromodulation can affect craving and self-regulation but overcomes the limitations of static stimulation paradigms by engaging dynamic, frequency-tuned neural circuits (Vosskuhl et al., 2018; Song et al., 2019; Mehta et al., 2023). Through targeting theta and alpha oscillations in functionally distinct regions, we aim to dissect the mechanistic underpinnings of craving modulation and inform the development of targeted neuromodulatory interventions for obesity and compulsive eating behavior.

The primary aim of this study is to evaluate whether tACS targeting the DLPFC, ACC, or insula can modulate craving-related oscillatory activity and enhance inhibitory control in individuals with varying degrees of food addiction. We hypothesize that theta-frequency stimulation of the ACC and insula will strengthen inhibitory control mechanisms and interoceptive awareness, while alpha-frequency stimulation of the DLPFC will enhance top-down cognitive regulation. By investigating these site- and frequency-specific effects, this study seeks to advance our mechanistic understanding of craving-related network dynamics and inform the development of non-invasive neuromodulatory interventions for compulsive eating behavior.

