#### 2.2.5 Sample size and power considerations

The sample size was calculated based on prior studies investigating neuromodulation effects on craving-related behavior and oscillatory activity (Song et al., 2019, 2022; Althubaiti, 2022; Kim et al., 2023; Gairola et al., 2024; Arifin and Yaacob, 2025; Sánchez-Garrido Campos et al., 2025). Assuming a moderate effect size (Cohen’s f = 0.25), an alpha level of 0.05, and a desired power of 0.80, a minimum of 35 participants per group is required to detect statistically significant differences in the primary behavioral outcome.

To account for potential attrition and non-compliance, a 20% dropout rate was incorporated into the calculation, yielding a final target of 175 participants distributed across the five study groups. This includes 140 participants in the FA+ parallel groups and 35 in the FA- crossover group.

Given the multimodal nature of data collection, including repeated electroencephalography (EEG) and functional magnetic resonance imaging (fMRI) measurements, a sensitivity analysis was also conducted. This analysis confirmed that the study remains adequately powered to detect within-subject changes in neural and behavioral outcomes while maintaining sufficient statistical power for between-group comparisons.

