Data management will be conducted in accordance with ethical data protection standards. All data will be stored on a secure, encrypted server with access limited to authorized personnel. Personal identifiers will be removed and replaced with anonymized participant codes. Missing data will be handled using multiple imputations via chained equations (MICE), assuming data are missing at random. Sensitivity analyses will be conducted to test the robustness of findings under different imputation models.

All statistical analyses will follow an intention-to-treat approach. The primary outcome–change in S-FCQ and FCI scores–will be analyzed using repeated measures ANOVA, with time (pre/post) and group (stimulation target and sham) as factors. *Post hoc* comparisons will be corrected using the Bonferroni method. Changes in Go/No-Go performance will be analyzed using ANCOVA, adjusting baseline reaction times and error rates. EEG parameters will be analyzed using linear mixed-effects models to account for within-subject correlations across sessions. Functional connectivity changes in fMRI will be assessed using seed-based and ICA models, with between-group comparisons conducted using *t*-tests or mixed models where appropriate. Longitudinal changes in YFAS and T-FCQ scores will be modeled using hierarchical linear regression.

Exploratory analyses will examine whether individual differences in sex, BMI, and baseline craving severity moderate the effects of tACS. Clustering methods will also be used to identify subgroups based on EEG and fMRI response profiles.

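### The article gives conflicting accounts of what is primary and when it is measured, while the sample size rests on one unnamed outcome at alpha 0.05

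*Protocol article*

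**What the plan says.** The article describes the primary outcome in four places, and they do not match.

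- **Abstract (Methods) and Section 2.4.** Two domains are primary: "The primary outcomes of this study are changes in food craving intensity and inhibitory control following the tACS intervention". Section 2.4 assigns S-FCQ and FCI to craving and the Go/No-Go task to inhibitory control, which makes at least three measures.
- **Section 2.5.** The primary outcome, in the singular, is the change in S-FCQ and FCI. Go/No-Go follows with its own ANCOVA and is not called primary.
- **Section 2.2.5.** The calculation uses one alpha: "Assuming a moderate effect size (Cohen’s f = 0.25), an alpha level of 0.05, and a desired power of 0.80". It concludes that "a minimum of 35 participants per group is required to detect statistically significant differences in the primary behavioral outcome". No instrument is named.
- **Section 1.** The primary aim is to learn whether stimulation "can modulate craving-related oscillatory activity and enhance inhibitory control in individuals with varying degrees of food addiction". The Abstract and Section 2.4 place oscillations among the secondary outcomes.

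Timing differs too. The opening of Section 2.4 has the behavioral measures before and after stimulation on Days 1 and 5. The Figure 1 caption and Section 2.5 (data collection) add Day 8. The analysis text in Section 2.5 has only a two-level pre/post time factor.

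On multiplicity, the article says only that post hoc "comparisons will be corrected using the Bonferroni method". That sentence follows the repeated measures ANOVA of the craving scales.

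**The concern.** Inhibitory control is primary in Section 2.4 and not in Section 2.5, and the sample size allows for only one outcome. An analysis plan written later could not honour all three statements. Until they are reconciled, a registry entry could list different primary sets, each with support in the article, and the headline result could be chosen after the data are seen.

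The Bonferroni step, as placed, handles comparisons between groups within an outcome. It does not handle a trial that may claim success on S-FCQ, on FCI or on Go/No-Go. If any one of these would do, the false positive rate for the primary claim is above the 5% used in the power statement.

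**Working it through.** **1. The plan's own figure.** Inputs from Section 2.2.5: f = 0.25, alpha 0.05, power 0.80, 35 per group. The section does not name the test, so several were tried.

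- One-way ANOVA, 4 groups: 45 per group needed; power at 35 is 68%.
- Group-by-time interaction, 4 groups, at least 2 measurements: at most 23 per group needed.
- Between-group test with repeated measures, k = 4 groups, m = 2 measurements, assumed correlation 0.5 between measurements. The noncentrality is f² × N × m / (1 + (m − 1) × 0.5), on k − 1 and N − k degrees of freedom. At N = 136 this is 0.0625 × 136 × 2 / 1.5 = 11.33, and 34 per group suffices. At 35 per group (N = 140) power is 82%.

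The last variant comes close to the stated 35. In it, all of alpha 0.05 goes to one outcome.

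**2. Chance of at least one false positive.** Two assumptions, neither stated in the article: each measure is tested at 0.05, and success on any one counts. For m independent measures the chance is 1 − 0.95^m:

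- m = 2: 1 − 0.9025 = 9.8%
- m = 3: 1 − 0.8574 = 14.3%
- m = 4: 1 − 0.8145 = 18.5%

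The article gives no correlation between measures, so a range was simulated in two ways: overall F tests with 4 groups of 35, and two-sided z tests. Where the two differ, both results are shown.

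| Measures | r = 0 | r = 0.5 | r = 0.7 | r = 0.9 |
|---|---|---|---|---|
| 2 (S-FCQ, FCI: Section 2.5) | 9.8% | 9.1–9.2% | 8.3–9.0% | 7.1–7.4% |
| 3 (adding Go/No-Go: Section 2.4) | 14.3% | 12.4–12.5% | 10.9–11.1% | 8.4–8.7% |
| 4 (Go/No-Go as reaction time and errors) | 18.5% | 15.5–15.6% | 13.1–13.7% | 9.3–9.7% |

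This is one test per measure. Reading Days 1, 5 and 8 as separate primary tests would raise the figures.

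**3. Cost of splitting alpha.** Same test variant as the one that comes close to 35 per group:

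| Primary measures | Alpha each | n per group for 80% power | Power at 35 per group |
|---|---|---|---|
| 1 | 0.05 | 34 | 82% |
| 2 | 0.025 | 40 | 73% |
| 3 | 0.0167 | 44 | 68% |

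For three independent measures at 0.0167 the overall error is 1 − (1 − 0.0167)³ = 4.9%. With a 20% dropout allowance, 44 per group becomes 44 / 0.8 = 55. A single named primary, or a fixed testing order, leaves the first test at 0.05 and needs no increase for multiplicity.

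**The case against.** The strongest reply is that this is a condensed article. A testing order or alpha split is commonly left to an analysis plan, and none is shown. Section 2.5 might also be using its label loosely for the craving half of Section 2.4. This has force against any complaint that a multiplicity rule is absent. It does not remove the conflict between Sections 2.4, 2.5 and 2.2.5, because a later plan would have to override at least one of them.

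Three further objections stand and limit the point.

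- The article never says that each measure is tested at 0.05 or that one success is enough. The single alpha in Section 2.2.5 belongs to the sample size. If every measure had to succeed, there would be no inflation.
- The case for a fourth endpoint is thin. Section 2.5 mentions reaction times and error rates as baseline adjustments in the ANCOVA. Analysing them as two separate endpoints is plausible but not stated.
- The Introduction describes an aim, not an outcome list. It adds to the inconsistency but is weaker evidence than Section 2.4, and it does not make oscillations a primary outcome.

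**Conclusion.** The conflict over what is primary, and at which time point, is in the text and should be resolved. The error rate is a conditional consequence: about 7–10% under the two-scale definition, about 8–14% under the three-measure definition, and up to 18.5% with four independent endpoints. All of these assume separate tests at 0.05, any one success counting, and correlations between 0.9 and 0.

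A reader might infer that the trial's false positive rate is 11–18% outright. The documents do not support that. The range takes both unstated rules as given, leaves out the two-scale definition in Section 2.5 and the higher correlations, and needs the doubtful fourth endpoint to reach its top. A reader might also infer that the power statement refers to S-FCQ. Section 2.2.5 names no instrument, and FCI or Go/No-Go would fit its wording equally well.

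**What to change.** Before registration, which Section 4 places ahead of enrollment:

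1. Name one primary measure and one time point or contrast. S-FCQ is one reasonable choice; another named measure would also serve.
2. Test the remaining primary measures in a fixed order at 0.05, for example one named Go/No-Go measure and then FCI. Let the overall group comparison decide each step, and keep the Bonferroni step for contrasts within it. Alternatively, split alpha across the primary measures and restate the power at the reduced level.
3. Use the same list in the Abstract, the Introduction's primary aim and Sections 2.2.5, 2.4 and 2.5, and have the power statement name the chosen measure.

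The fixed order costs no participants, but measures lower in the order are confirmatory only if those above succeed. On the assumptions above, splitting alpha over three measures costs either power (82% to 68% at 35 per group) or size (44 per group). Either way, the changed outcome wording must go to the ethics committees, to which the study has already been submitted (Sections 2.2.4 and 4).
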